## 12. HRQOL (HEALTH-RELATED QUALITY OF LIFE)

| #  | Outcome Measures          | Control | Intervention | Delta |
|----|---------------------------|---------|--------------|-------|
| 8a | xxi. EQ-5D-5L             |         |              |       |
|    | Index score               | X       | X            | X     |
|    | VAS                       | X       | X            | X     |
| 8b | xxii. HADS                |         |              |       |
|    | • Anxiety (continuous)    | X       | X            | X     |
|    | • Depression (continuous) | X       | X            | X     |
| 8c | xxiii. EORTC-QLQ-CR29     |         |              |       |
|    | 29 individual items       | X       | X            | X     |

### 12.1 xxi. EQ-5D-5L

This secondary outcome is displayed by timepoint. The information to calculate it is derived from the CRF EQ-5D-5L. It is in two parts: a summary index value derived from the code, and a visual analogue scale score (VAS). Instructions for calculating these values are given in the appendices.

- The EQ-5D-5L summary index value ranges from less than 0 (indicating a health state worse than death) to 1 (indicating full health). Higher scores represent better health states.
- The EQ-5D-5L Visual Analogue Scale (VAS) ranges from 0 to 100. The maximum value is 100 and represents the best health you can imagine. The minimum value is 0 and represented the worst health you can imagine.

We will treat both variables as scores and continuous variables. The scoring rules are in the appendices.

### 12.2 xxii. HADS (anxiety)

This secondary outcome is displayed as both a continuous and categorical variable. The information to calculate it is derived from the CRF HADS and Pre-Surgery Questionnaire. It is a score. The scoring rules are in the appendices. The continuous version is detailed here. The other variants are detailed in the subgroup analysis.

- Continuous. The continuous version of this variable will be a number derived from that score. It will be modelled as a continuous variable

### 12.3 xxii. HADS (depression)

This secondary outcome is displayed as both a continuous and categorical variable . The information to calculate it is derived from the CRF HADS and Pre-Surgery Questionnaire. It is a score. The scoring rules are in the appendices. The continuous version is detailed here. The other variants are detailed in the subgroup analysis.

- Continuous. The continuous version of this variable will be a number derived from that score. It will be modelled as a continuous variable

### 12.4 xxiii. EORTC-QLQ-CR29

This secondary outcome is displayed by timepoint. The information to calculate it is derived from the CRF EORTC QLQ - CR29. It is a continuous variable and a score. The scoring rules are in the appendices. The score will be calculated for the 29 individual items. The 29 individual items will be descriptive only

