### 4.2 Output variables

We expect to model all secondary outcome variables, except survival, recurrence, new primary/secondary cancer, re-admission rates, re-operation rates, costs and resource use, and adverse events. The final decision will depend on the available data. For example, if the counts for conversion to open surgery rates are very low, we will not model this outcome.

Therefore, we plan on analysing:

- Morbidity (five variables not including 2iii survival)
- Operative outcomes (seven variables not including re-operation and re-admission rates)
- Hospital stay (two variables)
- Anthropometry (two variables)
- Fitness (one variable)
- Health-related quality of life (HRQoL) (three variables)

That's twenty variables equating to at least 20 models, as some of those variables will be further subdivided (eg HRQoL variable "EQ-5D-5L" has two subdivisions, index and VAS).

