#### 17.2 EORTC-QLQ-CR29

- Sources: [https://drive.google.com/file/d/16j3pr9bEYVBra2tMp6B\\_2QLnxJ85kaDP/view](https://drive.google.com/file/d/16j3pr9bEYVBra2tMp6B_2QLnxJ85kaDP/view)  
<https://www.eortc.org/app/uploads/sites/2/2018/08/Specimen-CR29-English-2.1.pdf>  
<https://www.ncbi.nlm.nih.gov/pmc/articles/PMC6541702/>
- Online calculator: [https://score.awellhealth.com/calculations/eortc\\_qlq\\_cr29](https://score.awellhealth.com/calculations/eortc_qlq_cr29)

The EORTC QLQ-CR29 is a patient-reported outcome measure to evaluate health-related quality of life among colorectal cancer (CRC) patients in research and clinical practice. For the scoring rules see here: [https://drive.google.com/file/d/16j3pr9bEYVBra2tMp6B\\_2QLnxJ85kaDP/view](https://drive.google.com/file/d/16j3pr9bEYVBra2tMp6B_2QLnxJ85kaDP/view) .

The questionnaire includes 29 items, numbered 31 to 59. They are divided into two categories: items about symptoms (gastrointestinal, urinary, pain and others) and items about functions (sexual, body image and others) that are associated with CRC and its treatments. There are separate versions of items 49 to 54 for people with and without stomas, and item 55 is only for patients with a stoma. Items 56 and 57 are for men only, and items 58 and 59 are for women only.

All the QLQ-CR29 questions except one (item 48 requires a yes or no answer) have four possible answers. They are

- Not at all (1)
- A little (2)
- Quite a bit (3)
- Very much (4)

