**Table: EORTC-QLQ-CR29 Functional Scales (0 is bad, 100 is good)**

| Scale                   | Scale name | Number of items | Item #   | Question # | 100 score at      |
|-------------------------|------------|-----------------|----------|------------|-------------------|
| Body_image              | BI         | 3               | 15,16,17 | 45,46,47   | Not at all (1)    |
| Anxiety                 | ANX        | 1               | 13       | 43         | Not at all (1)    |
| Weight                  | WEI        | 1               | 14       | 44         | Not at all (1)    |
| Sexual_interest_(men)   | SEXM       | 1               | 26       | 56         | Very much (4) [1] |
| Sexual_interest_(women) | SEXW       | 1               | 28       | 58         | Very much (4) [1] |

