**Table: EORTC-QLQ-CR29 Symptom scales (0 is good, 100 bad)**

| Scale                    | Scale name | Number of items | Item # | Question # | 100 score at  |
|--------------------------|------------|-----------------|--------|------------|---------------|
| Urinary_frequency        | UF         | 2               | 1,2    | 31,32      | Very much (4) |
| Blood_and_mucus_in_stool | BMS        | 2               | 8,9    | 38,39      | Very much (4) |
| Stool_frequency*         | SF         | 2               | 22,23  | 52,53      | Very much (4) |
| Urinary_incontinence     | UI         | 1               | 3      | 33         | Very much (4) |
| Dysuria                  | DY         | 1               | 4      | 34         | Very much (4) |
| Abdominal_pain           | AP         | 1               | 5      | 35         | Very much (4) |
| Buttock_pain             | BP         | 1               | 6      | 36         | Very much (4) |
| Bloating                 | BF         | 1               | 7      | 37         | Very much (4) |
| Dry_mouth                | DM         | 1               | 10     | 40         | Very much (4) |
| Hair_loss                | HL         | 1               | 11     | 41         | Very much (4) |
| Taste                    | TA         | 1               | 12     | 42         | Very much (4) |
| Flatulence*              | FL         | 1               | 19     | 49         | Very much (4) |
| Faecal_incontinence*     | FI         | 1               | 20     | 50         | Very much (4) |
| Sore_skin*               | SS         | 1               | 21     | 51         | Very much (4) |
| Embarrassment*           | EMB        | 1               | 24     | 54         | Very much (4) |
| Stoma_care_problems      | STO        | 1               | 25     | 55         | Very much (4) |
| Impotence                | IMP        | 1               | 27     | 57         | Very much (4) |
| Dyspareunia              | DYS        | 1               | 29     | 59         | Very much (4) |

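### EORTC-QLQ-CR29 is planned only as 29 separate items, so the four multi-item scales defined in the supplement's own scoring appendix are never produced

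*Combined protocol and SAP*

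**What the plan says.** All references are to the SAP supplement on secondary outcomes unless stated otherwise.

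- **Section 12.4** describes the EORTC-QLQ-CR29 thus: "It is a continuous variable and a score". It adds "The scoring rules are in the appendices", and then fixes the unit of scoring: "The score will be calculated for the 29 individual items. The 29 individual items will be descriptive only".
- **The outcome list in section 5 and the results table at the head of section 12** each give the instrument one row, for the 29 items. Section 5 marks that row as not to be modelled.
- **Appendix 17.2**, on the number of items: "The questionnaire includes 29 items, numbered 31 to 59". It then sets out two tables of scales, headed "Table: EORTC-QLQ-CR29 Functional Scales (0 is bad, 100 is good" and "Table: EORTC-QLQ-CR29 Symptom scales (0 is good, 100 bad", and names the items in each scale. It singles out one question: "item 48 requires a yes or no answer".
- **Section 4.2**, in its list of what will be modelled, includes "Health-related quality of life (HRQoL) (three variables".
- **Protocol synopsis, section 9.8 and Appendix B** place the instrument at the 30-day post-operative assessment only.

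**The concern.** Section 12.4 sends the reader to the appendix for scoring rules but then plans outputs that do not use the scales found there. The other two quality-of-life instruments are not treated in this way: HADS is reported as two seven-item subscales, not 14 items, and EQ-5D-5L as an index and a VAS, not five dimensions.

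The EORTC-QLQ-CR29 is the trial's only colorectal-specific quality-of-life measure, and it sits under an objective to report differences between the arms. If the plan is followed as written, the report will contain no score for four of the instrument's scales. Anyone who uses it to plan the definitive trial will have no SD for them. An analyst must also guess whether the instrument is modelled and what to do with the stoma-bag question.

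**Working it through.** **1. Count of items and scales (tables in 17.2).** Items 31 to 59: 59 − 31 + 1 = 29, which agrees with the stated number.

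| Group | Scales | Items |
|---|---|---|
| Functional | 5 | 3 + 1 + 1 + 1 + 1 = 7 |
| Symptom | 18 | 2 + 2 + 2 + 15 × 1 = 21 |
| Total | 23 | 28 |

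The 28 items are each used once. The only one left over is item 48.

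**2. Which scales are lost.** The multi-item scales are body image (45–47), urinary frequency (31–32), blood and mucus in stool (38–39) and stool frequency (52–53): four scales and 3 + 2 + 2 + 2 = 9 items. The other 23 − 4 = 19 scales are identical to their items, so item scoring yields them exactly. None of the four has a row in section 5 or section 12.

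**3. What can be rebuilt from item results.** Take answers 1, 2 and 4 on items 45–47. The appendix's conversion, with 100 at the lowest response, gives item scores of 100, 66.7 and 0. Their mean is 166.7 / 3 = 55.6, the body-image score. The items are therefore converted correctly but not combined. With complete answers, a scale mean is the mean of its item means. The SD is different. For k items with equal SD and a common correlation r,

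scale variance / item variance = (1 + (k − 1)r) / k.

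| | r = 0 | r = 0.4 | r = 0.7 | r = 1 |
|---|---|---|---|---|
| k = 2 | 0.50 | 0.70 | 0.85 | 1.00 |
| k = 3 | 0.33 | 0.60 | 0.80 | 1.00 |

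The documents give no inter-item correlations. With item SDs alone, and r anywhere from 0 to 1, the variance is uncertain by a factor of two (two items) or three (three items), and so is any sample size proportional to it. If r is assumed to be 0.4 to 0.7, the ratios are 0.70–0.85 and 0.60–0.80. This range is an illustration, not a figure from the plan.

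**4. Item 48.** Three entries set it apart: the text of 17.2 exempts it from the four-answer format, the 0–100 conversion is stated for the four levels only, and the question table gives it two levels and no scale. Two entries pull it back in: section 12.4 calculates a continuous score for all 29 items, and the question table's cell for the answer that scores 100 names the fourth response level, which a yes/no question does not have.

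**5. Denominators.** No participant answers all 29 items. Each sex skips two, and item 55 is for people with a stoma: 29 − 2 = 27 items with a stoma, 26 without. Each skipped item is a scale of its own, so 23 − 2 = 21 scales apply with a stoma and 20 without.

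**6. Modelled or not.** Section 4.2 reaches its total as 5 + 7 + 2 + 2 + 1 + 3 = 20. Its groups are counted by the synopsis numerals: the seven operative outcomes are vii to xiii, although section 5 splits three of them into two rows each. On that basis the three quality-of-life variables are xxi, xxii and xxiii, and xxiii is the EORTC-QLQ-CR29. It is also absent from section 4.2's list of outcomes that will not be modelled. Sections 5 and 12.4 say the opposite.

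**7. Timepoints.** The section 5 cell for this instrument repeats the entry above it, which covers baseline, pre-operative assessment 3 and 30 days. The protocol collects it at 30 days only.

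**The case against.** The strongest reply is that little is at stake. This is a secondary outcome with no baseline, reported descriptively in a feasibility trial whose sample size rests on the progression criteria and which will report no p-values. Nineteen of the 23 scales are unaffected, every raw item is kept, and the four scales can be derived at any time. All of that stands, and it limits the weight of the point.

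Three stronger readings are tempting, and the documents do not support them.

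- *That item 48 will be scored from 0 to 100, giving 0 or 33.* That needs yes/no to be coded 1/2 and passed through the four-level conversion, which no section directs. What the supplement contains is a contradiction, not a rule.
- *That the plan yields no between-arm comparison or SD at all.* The section 12 table has a difference column for the item row, and supplement section 24 carries over the protocol's means, SDs and confidence intervals for continuous variables. What is missing is a score and SD for four scales.
- *That nine items are mis-scored.* Each is converted correctly; they are simply not aggregated.

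It is also fair to object to adjusted models for all 23 scales. With at most 72 patients, several scales confined to subsets and 19 of them single four-level items, that would be a poor trade. Section 4.2 in any case leaves modelling dependent on the data, and descriptive reporting is a legitimate choice.

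The timepoint entry is clerical, since the repeated cell is labelled for xxi and xxii only. One could also read the three variables in section 4.2 as EQ-5D-5L and the two HADS subscales, but this departs from how the other groups are counted and does not explain the missing exclusion.

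**Conclusion.** The point holds. The supplement defines 23 scales and plans to report 29 items, so four multi-item scales covering nine items are never produced and their SDs cannot be recovered from published item SDs. Around this are three smaller inconsistencies: the status of item 48, whether the instrument is modelled, and its timepoints.

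The scale and item counts rest on the supplement's tables alone. The two- to threefold uncertainty in variance assumes equal item SDs and a common, non-negative correlation. No efficiency gain should be claimed beyond the assumed range shown. The consequence is confined to one secondary, descriptive outcome. No progression criterion or primary result changes, and the data needed are already in the collection schedule.

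**What to change.** In the supplement:

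- **Sections 5, 12 and 12.4:** replace the 29-item row with the 23 scales from 17.2, at 30 days only, each with mean, SD and between-arm difference with 95% CI, labelled descriptive. Item-level results can go in an appendix table.
- **Section 17.2:** state in the text how items are combined into a scale score and what happens when an item of a multi-item scale is missing. At present it only links to outside rules, and section 15.1 says that missing data are not imputed. Give denominators for the stoma-only and sex-specific scales.
- **Item 48:** report it as a yes/no count, use it to select the stoma or non-stoma wording, and correct its cell in the question table.
- **Section 4.2:** bring it into line with section 5. If the instrument stays descriptive, name it among the outcomes not modelled and reduce the count to 5 + 7 + 2 + 2 + 1 + 2 = 19.

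The cost is some wording, one decision on missing items and a short scoring script. No new data are needed, and the main table falls from 29 rows to 23 plus one count.

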## 13. COSTS AND RESOURCE USE

These outcomes will be calculated as part of the health economics section of the trial and are, therefore, not covered in this document.

## 14. ADVERSE EVENTS

| #   | Outcome Measures      | Control | Intervention | Delta |
|-----|-----------------------|---------|--------------|-------|
| 10a | xxvii. Adverse events | X       | X            | X     |

### 14.1 xxvii. Adverse events

The information to calculate it is derived from CRF Adverse Events (any time). It is a categorical variable & each category is a count/rate (0-n/%).

| #   | Outcome Measures                                     | Control | Intervention | Delta |
|-----|------------------------------------------------------|---------|--------------|-------|
| 10b | xxvii. Adverse events (by severity)                  |         |              |       |
|     | N of AEs in category Mild                            | X       | X            | X     |
|     | N of AEs in category Moderate                        | X       | X            | X     |
|     | N of AEs in category Serious                         | X       | X            | X     |
| 10c | xxvii. Adverse events (by seriousness)               |         |              |       |
|     | N of AEs in category Serious                         | X       | X            | X     |
|     | N of AEs in category Non-serious                     | X       | X            | X     |
| 10d | xxvii. Adverse events (misc)                         |         |              |       |
|     | N of people with at least one AE                     | X       | X            | X     |
|     | N of people with at least one moderate AE            | X       | X            | X     |
|     | N of people with at least one serious AE             | X       | X            | X     |
|     | N of people with at least one SAE                    | X       | X            | X     |
|     | N of people with at least one moderate AE and/or SAE | X       | X            | X     |

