One in 5 people experience an adverse, mostly mild, event due to the intervention.[21] Constipation (1 in 7), fatigue (1 in 12), headache (1 in 17), and dizziness (1 in 22) are the most common Adverse events (AEs) albeit mild (only 11% were moderate or severe), reduce in intensity over time and disappear as soon as the intervention is discontinued.[21, 22] Here, the risk of constipation will be proactively managed with advice for high energy-free fluid intake (>2.5 litres/day) and a fibre supplement.

Participants will receive the intervention on top of the local standard care pathway that may include advice and support on pre-habilitation.

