#### **10.1. Definition of Serious Adverse Events**

A serious adverse event is any untoward medical occurrence that:

- results in death
- is life-threatening
- requires inpatient hospitalisation or prolongation of existing hospitalisation
- results in persistent or significant disability/incapacity
- consists of a congenital anomaly or birth defect.

Other 'important medical events' may also be considered a serious adverse event when, based upon appropriate medical judgement, the event may jeopardise the participant and may require medical or surgical intervention to prevent one of the outcomes listed above.

NOTE: The term "life-threatening" in the definition of "serious" refers to an event in which the participant was at risk of death at the time of the event; it does not refer to an event which hypothetically might have caused death if it were more severe.

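### The adverse-event severity table ends in Serious rather than Severe, and the composite row omits severe non-serious events

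*Combined protocol and SAP*

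**What the plan says.** The supplement's section 14.1 has three detailed blocks for adverse events by arm.

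- **10b**, headed "xxvii. Adverse events (by severity)", counts events as mild, moderate, and then "N of AEs in category Serious".
- **10c**, headed "xxvii. Adverse events (by seriousness)", has that same serious row and "N of AEs in category Non-serious".
- **10d** counts people. It opens with "N of people with at least one AE", then has separate rows for a moderate AE, a serious AE and an SAE, and ends with "N of people with at least one moderate AE and/or SAE".

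The protocol keeps the two scales apart. Section 10.1 defines a serious event by what it leads to; one of its criteria is that the event "requires inpatient hospitalisation or prolongation of existing hospitalisation". Section 9.6.1 grades earlier diet-related events by intensity and says that "only 11% were moderate or severe".

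**The concern.** Severity is how intense an event is. Seriousness is whether it met one of the listed outcomes. An event can be severe without being serious, and an SAE can be of moderate intensity. Block 10b uses a seriousness term as the top grade of a severity scale, so two analysts could fill in the same table differently from the same data.

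This is the only detailed adverse-event table layout in the documents. SAP section 6.7 on harms only refers to other sections, and the independent repeat analysis listed in SAP Table 4 covers criteria 1a to 1c and 2 to 4 but not safety, so that check would not necessarily catch the problem. Operative and post-operative complications are reported as outcomes and not as AEs (protocol section 10). The AE tables therefore mainly describe how the diet was tolerated before surgery, where the intensity of events is useful information.

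**Working it through.** The plan states no figure on this point, so there is none to reproduce. The check has two parts.

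**1. The rows set against each other.** Take an invented set of 12 events in 12 different people: 9 mild, 1 moderate, 1 severe but non-serious, and 1 SAE of severe intensity.

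| | Literal reading (third row = SAEs) | Slip reading (third row = severe) | After the fix |
|---|---|---|---|
| 10b third row | 1 | 2 | 2 |
| 10b total | 9 + 1 + 1 = 11 | 9 + 1 + 2 = 12 | 12 |
| 10c serious row | 1 | 1 | 1 |
| 10c total | 1 + 11 = 12 | 12 | 12 |
| 10d last row (people) | 1 + 1 = 2 | 1 + 1 = 2 | 1 + 1 + 1 = 3 |

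- On the literal reading, 10b falls one short of 10c, because the severe non-serious event has no severity row.
- On the slip reading, the totals agree, but rows with the identical label show 2 in one block and 1 in the next. Someone taking the first as a count of SAEs would see too many.
- On both readings, the 10d composite counts the person with the moderate event and omits the person with the severe non-serious one.
- In all three columns the total number of events (12), SAEs (1) and people with any AE (12) are the same. The severe non-serious event is always within the non-serious row of 10c.

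**2. How many events could be involved.** Inputs: 36 participants in the intervention arm (protocol 11.3); from protocol 9.6.1, 1 in 5 people with a diet-related event, frequencies of 1/7, 1/12, 1/17 and 1/22 for the four commonest events, and 11% moderate or severe.

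- Counting people: 36 × 1/5 = 7.2. At one event each, 7.2 × 0.11 = 0.79 moderate-or-severe events.
- Counting the four listed events: 36 × (1/7 + 1/12 + 1/17 + 1/22) = 11.9, and 11.9 × 0.11 = 1.31.

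These totals include moderate events, which already have their own rows. The severe part is not given. If it is assumed to be between 10% and 50%, the expected number of severe events runs from 0.79 × 0.10 = 0.08 to 1.31 × 0.50 = 0.65. With a Poisson count, the chance of at least one is 1 − exp(−0.08) = 8% to 1 − exp(−0.65) = 48%.

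**The case against.** The strongest reply is that this is a slip of the pen. Block 10d lists a serious-AE row and an SAE row side by side, which is redundant unless the first means severe, and 10b is headed by severity with seriousness kept for 10c. On that view the severe rows exist under the wrong name, 10b is exhaustive and 10d has no duplicate. I think this is the likelier intention. It does not clear the table: the shared label still misleads, and the composite row still lacks severe events. One could read moderate in that row as moderate or worse, but the same word stands for a single level in 10b. If the slip reading is right, the omitted participant would at least appear in the mislabelled severe row of 10d.

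The tables are also descriptive. The supplement's list of secondary outcomes says adverse events will not be modelled, so no estimate changes. The severity options on the adverse-event form are not in the documents, nor is the Data Definitions and Tables document that the SAP says should be read with it. How severity is recorded, and whether a moderate SAE would be entered in two rows, cannot be checked.

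A reader might go further and infer that the tables understate diet toxicity and so weaken the safety criterion for progression. The documents do not support that. SAP Tables 1 and 3 define criterion 5 from related AEs and related expected and unexpected SAEs, by type, number and percentage, with adjudication by committee. They use no severity grade and do not cite these blocks, which belong to a secondary outcome. The direction is not fixed either: severe non-serious events filed under the serious label would make the profile look worse. Nor do the documents suggest that severe reactions are what the diet mostly produces; protocol 9.6.1 describes the events as mostly mild.

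**Conclusion.** The point stands as a labelling error plus one gap in content. Block 10b mixes intensity with seriousness and can be filled in two ways. The 10d composite omits participants whose only notable event is severe and non-serious, on either reading. No event is lost from the tables as a whole; what can be hidden or misread is its grade.

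The size is small: about 0.8 to 1.3 moderate-or-severe events expected in the intervention arm, of which an unknown part is severe. That rests on the earlier diet data carrying over to this population; the 10% to 50% severe share is my assumption. The direction of any misstatement is uncertain, and no effect on criterion 5 is shown. It is worth correcting because it is a specified safety output and the correction costs almost nothing.

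**What to change.** In the supplement's section 14.1:

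1. Label the third row of 10b *Severe*.
2. In 10d, change the serious-AE row to *at least one severe AE*.
3. Change the last row of 10d to *at least one moderate or severe AE and/or SAE*.
4. Keep seriousness only in 10c and in the SAE row of 10d, and grade SAEs for severity on the same three levels so that 10b and 10c have the same total.
5. Check that the severity options on the adverse-event form match.

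The cost is three row labels and a check of the form. If the form already records severe, no new data are needed. If it does not, one option has to be added, and the report should say how events recorded before that were graded.
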